## Abstract

**Background:**

In the Netherlands, the prevalence of anxiety disorders is 20%; and children with anxiety are at increased risk for psychopathology throughout adulthood. Recently, a revised version of a cognitive behavioral therapy manualized program called 'Thinking + Doing = Daring' (TDD) was developed for children between 8 and 12 years old with an anxiety disorder. The main aim of this project is to conduct a Randomized Controlled Trial (RCT) to evaluate the effectiveness of TDD.

**Methods/Design:**

The CBT program will be tested with a RCT with 120 clinically anxious children (8-12 years old) referred to one of three mental health care agencies. Children will be randomly assigned to the experimental (*N *= 60, TDD) or to the control condition (*N *= 60, treatment as usual). The primary outcome measure will be the child's anxiety symptoms level. Secondary outcome measures will be externalizing (e.g. aggression) and internalizing problems (e.g. depression). Two potential mediators of change will be examined in the current study: therapeutic alliance and parenting. Mother and child in both the experimental and control condition will be surveyed at baseline, post treatment and after 6 and 12 months (follow-up). It is hypothesized that children in the experimental condition will show a stronger decrease in anxiety symptoms compared to children that receive treatment as usual. Moreover, we expect that a strong therapeutic alliance and decreases in parental control and rejection will contribute to treatment success.

**Discussion:**

Early treatment for anxiety problems has the potential to not only result in anxiety reductions, but also to prevent future problems such as substance abuse and psychopathology throughout adulthood. Our results will be immediately relevant to practice, since we are partnering with 'real world' community agencies. If the CBT program proves more effective than treatment as usual, it could be implemented in community mental health care agencies across the Netherlands and beyond. Moreover, it has the potential to make treatment in these community settings shorter, more efficient and therefore cost-effective. Trial registration: Nederlands Trial Register NTR2967

## Background

Anxiety disorders are one of the most common types of psychopathology during childhood [1]. In Europe, 12-20% of children experience anxiety [2]. More than 12% of the children is diagnosed with an anxiety disorder. In the Netherlands the prevalence of anxiety disorders is even higher than 20% [3,4]. Various forms of anxiety disorders exist. The most common anxiety disorders in childhood are the specific phobia, social anxiety disorder, separation anxiety and generalized anxiety [5].

A characteristic feature of all anxiety disorders in children is the preoccupation with danger. Although the type of stimulus eliciting fear may change over time due to developmental transformations, anxiety and fear are a chronic problem. In an attempt to cope with the perceived threat of the outside world children with anxiety disorders learn to avoid potentially threatening situations. As a result, the social and academic functioning of children with anxiety is jeopardized. Children with anxiety have fewer friends and receive lower grades at school [6]. Additionally, the importance of parental factors (e.g. genetic transmission, anxious modeling, over-controlling parenting style) in the etiology and maintenance of childhood anxiety is well established [7]. In turn, as a result of a child's anxiety family life can be impaired such that families with anxious children perceive more stress and participate less in social activities [6]. Finally, clinical levels of anxiety during childhood present great risks for future development, such as an increased risk for substance abuse and suicidality during adolescence [8] and higher rates of psychopathology and educational underachievement in adulthood [9,10]. Because of the high prevalence of anxiety in children and the detrimental effects on socio-emotional and academic functioning, which bear great challenges for future development, much research has been devoted to identifying effective interventions to target childhood anxiety.

Cognitive behavioral therapy (CBT) - with or without parental involvement - is consistently being identified as the most effective treatment for childhood anxiety. A recent meta-analysis among 24 studies found an overall posttreatment remission rate of anxiety disorders of 55.4% and showed a mean overall effect size of CBT is .86 [11]. All CBT treatments share similar ingredients such as exposure to anxious situations, cognitive restructuring of dysfunctional thoughts, relaxation before and during anxious situations and positive self-talk. In the Dutch context a protocollized CBT treatment for anxious children and adolescents called 'Thinking + Doing = Daring' (TDD) has been developed by [name] [12] based on these principles. Importantly, the intervention integrates parents by teaching them how to communicate with their child about anxious situations and how to motivate and support their child in overcoming its fear. Also the parent's own fears and anxieties are being discussed. The treatment consists of twelve weekly sessions with the child and three sessions with the parents. Three months after therapy, a follow-up session takes place.

In a study by Bodden, [name] and colleagues [13] the effectiveness of the TDD-treatment was tested with a randomized controlled trial including three different conditions. Children were between eight and 17 years old and either received the TTD (individual CBT with little parental involvement), a family CBT or were put on the waitlist for eight weeks. Some of the families in the waitlist condition received the treatment after eight weeks. These post waitlist results were included in the effect calculation. At post-treatment 41% of the children was free of all anxiety disorders and 56% was free of their primary anxiety diagnosis. All waitlist children still had anxiety disorders after the waitlist period. At three-month follow up these percentages were 52% and 67% respectively. Concerning the difference between the TTD and the family CBT, the study found better treatment outcomes for the TDD (56% recovered from anxiety) compared to the family CBT (28% recovered from anxiety). The effect size for the TDD was 1.39 and 1.03 for the family CBT (as measured with the parent version of the dutch version of the Screen for Child Anxiety Related Emotional Disorders (SCARED-NL). In families where parents had an anxiety disorder, children also benefited more from the TDD (46% recovered from anxiety at post treatment) compared to family CBT (19% recovered from anxiety at post treatment). Also, more dropouts were found in the family CBT-condition (19%) than in the TDD (3%). In sum, the effect sizes of the TDD program are promising and based on this study's results the TDD, that is an individual CBT with little parental involvement, seems to be more beneficial than a family CBT. The child and therapist manuals of the TDD are published including assessments and treatment integrity forms, and the program is now widely used in the Netherlands.

The primary aim of this study is to replicate and extend the findings of the Bodden et al study [13] in a randomized controlled trial. In contrast to the Bodden et al study [13] two conditions will be used: the experimental condition which will consist of the TDD program and the control condition which will consist of treatment as usual (TAU). The ultimate proof of the effectiveness of a treatment program is when it exceeds the effects of the treatment that families and children normally receive. Furthermore, to test the long-term effects of treatment six-month and 12-month follow up assessments will be conducted. Importantly, this study will take place in the real-world context, where co-morbidity is the rule rather than the exception [14]. In this way the study's results can be generalized to the context where the intervention may eventually be delivered, that is in mental health institutions in the Netherlands.

Finally, despite the promising results of CBT so far, variability in treatment outcomes remain. Not all children with anxiety profit from therapy. It is not clear why some children fail to show improvement in therapy, since we have little understanding of the underlying mechanisms and processes of change. Randomized controlled trials inform us *if *a certain interventions works but they do not tell us by what mechanism, information that is essential in order to further improve and tailor intervention efforts. Two potential mediators of change will be examined in the current study: therapeutic alliance and parenting.

Many researchers have confirmed the importance of alliance in adult therapy. Stronger therapeutic alliance predicts better outcome [15,16]. However, the role of alliance in child-therapy has received little attention so far and results are mixed. Kazdin [17] found that strong therapeutic alliance predicted more improvement in the child. However, in a study by Liber [18] alliance and treatment outcome were only moderately related. In two studies by Kendall [19,20] no significant association between alliance and treatment outcome were found. In the adult literature, alliance at one month after treatment has started is usually used to predict treatment outcomes [16]. However, alliance is likely to fluctuate across the treatment period. In order to test when alliance best predicts treatment outcomes, alliance will be assessed at multiple time points: one and two months after treatment has started and at post treatment.

The second potential mediator is parenting. Childhood anxiety is more common in families with anxious parents, suggesting a familial transmission of anxiety [21]. Numerous studies in previous years have focused on the influence of family interactions in the development, maintenance, and improvement of childhood anxiety (e.g. [22,23]) and found several potential parenting behaviors influencing childhood anxiety. The dimensions *rejection *and *control *received a great amount of consideration in the parenting literature (e.g. [24-26]), but with different definitions and mixed results. Recently, McLoad, Wood and Weisz [27] conducted a meta-analysis on both dimensions and found that both rejection (small effect) and control (medium effect) were associated with childhood anxiety. If treatment for childhood anxiety is effective, parent-child interactions are likely to change. In the current study, we will track changes in the dimensions rejection and control.

### Aim and hypotheses

The primary aim of the study is to evaluate the effectiveness of the CBT-program Thinking, Doing and Daring (TDD) by comparing it to treatment as usual (TAU). Our primary outcome, children's anxiety, will be assessed through parent reports and children's self-reports. To measure long-term effects of treatment, follow-up assessments at three month, six month and one year follow up will be conducted. The second aim is to analyze whether there are secondary positive outcomes beside recovery of anxiety. Secondary outcomes (e.g. depression, aggression) will be assessed through parent and teacher reports. The third aim is to analyze the potential mediating influence of alliance and parenting on positive treatment outcomes.

More specifically, we expect that a) children in the experimental condition will have significantly less anxiety symptoms after treatment and at the follow-up measurements than children who received treatment as usual, b) children who recover from an anxiety disorder will also show a significant reduction in secondary problem behavior (e.g. depression, aggression), c) children who form a strong alliance with their therapist will have less anxiety symptoms than children who form a less strong alliance, d) parent-child dyads for those children who improve through therapy will show less parental control and rejection after treatment than at the start of treatment.

## Methods/Design

### Trial design

The effectiveness of the TDD program will be tested in a RCT in which three Dutch community mental health agencies (Pro Persona Youth in Nijmegen and Arnhem and the Ambulatorium Nijmegen) will participate. A total of 120 clinically anxious children (8 - 12 years old) and their parents will participate in this study after filling in a consent form (see Figure 1 for the study design). The participants will be randomly allocated to the experimental (TDD, *N *= 60) or control condition (TAU, *N *= 60). The TDD consists of twelve weekly sessions with the child and three sessions with the parents. The treatment is supported with child, parent and therapist manuals. Children in the control group will receive the treatment that is usually delivered in those agencies. This means that these children will receive the treatment that the therapist considers to be the most effective treatment for that particular child. Baseline assessments, post-treatment, a six-month follow-up and a one year follow-up will be conducted among children, mothers and therapists and through direct observations (see Table 1).

**Figure 1 F1:**
[figure not shown]
**Flow chart of the phases of the randomized trial**.

**Table 1 T1:** Measurements collected at each wave

	Measurement waves					
	**Baseline/pre treatment**	**1 month**	**2 month**	**Post treatment**	**6 month follow-up**	**1 year follow-up**

SCARED-NL	X			x	x	x

CBCL	X			x	x	x

TRF	X			x	x	x

TASC		x	x	x		

WAI-s		x	x	x		

Parenting	X			x	x	x

To compensate for their time filling in the research questionnaires, parents will receive a financial contribution and children will receive little gifts (such as pens, stickers and small candy). Ethical approval has been granted by the ethical committee of the Faculty of Social Sciences at the Radboud University Nijmegen (ECG16122010).

### Participants

Child-participants between the age of eight to twelve years will be recruited at one of the agencies. As part of the usual intake procedure families are asked to fill in standard questionnaires to collect information for diagnostic assessment and indication criteria. When a child is between eight and twelve years old additional questionnaires will be administered. These are: the Child Behavior Checklist (CBCL), the Teacher Report Form (TRF) and the Screen for Child Anxiety Related Emotional Disorders (SCARED) and are meant to assess children's level of anxiety and to determine the presence of additional problems. Inclusion criteria are a score above the clinical cut-off on either the child or parent version of the SCARED-NL total scale or one of the following subscales: generalized anxiety, social anxiety, separation anxiety and panic disorder. Exclusion criteria are autism, post traumatic stress syndrome, specific anxiety disorder, obsessive-compulsive disorder and an IQ below 80. Medication is allowed and will be assessed during the measurement waves.

Families with an eligible child will be informed about the project by one of the researchers and will be asked to participate. When a family agrees to participate, they fill in an informed consent form. Families will be randomly allocated to the TDD or TAU condition using a blocked randomization scheme (block size 4). Randomization will be done by an independent researcher at the Behavioural Science Institute.

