### Therapists

All therapists (n = 16) participating in this study work at one of the three agencies. Two therapists are mental health workers and 14 therapists are graduated psychologists of which 12 have a registration as a Health Care psychologist ('GZ-psycholoog'). Seven therapists are between 25 and 40 years old. Five therapists are between 40 and 55 years old, and four therapists are older. Years of experience of the therapists varies between three and 27 years. At each institution the therapists will be randomly assigned to the experimental or control condition. The therapists in the experimental condition will participate in a two-day training in the protocol provided by the author of the manualized protocol, [name]. In this training the protocol will be explained and practiced on each other during exercises and role-plays. The therapist in the control condition will receive no extra training.

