The possible mediator parenting will be assessed through observations of structured mother-child interactions [42,43], taking place in the homes of the families at a time convenient for them. Interactions will be videotaped and subsequently coded for the dimensions rejection and control. In the study the focus is on mothers, since they are in most cases the primary caregiver and we want to standardize across participants and measurement waves. A standardized paradigm will be used for observations of mother-child interactions. Mother and child will engage in three 5-minute episodes: (1) a competitive sports game on the Nintendo Wii console, (2) a discussion about something the child is anxious about in the coming week, and (3) a cooperative sports game on the Nintendo Wii console The digital video recordings will be coded using Noldus Observer XT. Three assistants will be trained to reliably code videos for the dimensions rejection and control. Assistants will be intensively trained to a minimum criterion of 75% agreement and 0.65 kappa using a frequency/sequence-based comparison and a criterion of 80% agreement using a duration/sequence based comparison. Recalibration training will be conducted to minimize coder drift. A second coder for reliability purposes will code 20% of all sessions. Coders will be blind to which sessions will be used to assess observer agreement and also blind to the condition and when in the treatment protocol the observations were collected (pre, post or follow-up).

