### Sample size calculation

The study aims to assign 120 anxious children to the project. The children will be equally divided across both conditions. Power analysis (G-power) is based on a 3-month effect size of 1.0 taking into account a maximum of 20% attrition over time and loss of power due to multiple imputation. Sample sizes will be 60 families per condition (alpha < .05, power = .80). For testing the effect of the potential mediators, we do not need to run a RCT per se. However, as we are the first running a follow-up study on Bodden et al. [13], it is essential to establish whether we will obtain similar effect sizes. Hence, we can not estimate the variability in the mediators beforehand - as this has not been examined in these kinds of CBT treatments before - but previous work on other types of pathology [44] and the high effect size necessary to examine differences at all, provide us with confidence that our design and sample size is suitable. The sample sizes are large for observational treatment studies involving parent-child interactions [45]. Excellent observational studies with similar or smaller sample sizes have been published in top-tier journals. This is largely due to the fact that micro-coding in observational designs holds repeated measurements of individual variables [46].

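### One published block size of 4, in a trial whose treatments cannot be masked, would let a recruiter who can follow the list know up to a third of allocations in advance

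*Protocol article*

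**What the plan says.** The allocation method for children is in the protocol article under Participants: "Families will be randomly allocated to the TDD or TAU condition using a blocked randomization scheme (block size 4". The same section has consent before allocation and adds a safeguard: "Randomization will be done by an independent researcher at the Behavioural Science Institute". Recruitment is by study staff: "Families with an eligible child will be informed about the project by one of the researchers and will be asked to participate".

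Trial design gives a 1:1 ratio: "The participants will be randomly allocated to the experimental (TDD, *N *= 60) or control condition (TAU, *N *= 60". It names the sites: "three Dutch community mental health agencies (Pro Persona Youth in Nijmegen and Arnhem and the Ambulatorium Nijmegen) will participate".

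Therapists are handled separately: "At each institution the therapists will be randomly assigned to the experimental or control condition". Only those assigned to TDD get the two-day training (Therapists), and TDD comes with its own child and parent workbooks (Experimental condition). Blinding is described only for the video coders, who are "also blind to the condition and when in the treatment protocol the observations were collected (pre, post or follow-up". The primary outcome, SCARED-NL, is completed by child and mother (Outcomes).

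The article does not say whether the children's list is one list or one per agency, or whether the researchers who approach families see earlier allocations.

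**The concern.** Blocks of a known fixed size balance the arms at a price: once enough of a block has been seen, the rest is forced. That matters little where treatment is masked, because past allocations stay hidden. Here they do not. Each therapist works in one arm, so knowing who treats a child reveals that child's arm.

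An independent researcher keeps the list from being read. This does not stop the next entry being inferred from earlier ones when the block size is in print. Because families are approached before allocation, a recruiter who expects a particular arm could choose whom to approach, when to approach them, or how hard to persuade them. Intention-to-treat analysis keeps every randomised child in the analysis but cannot undo selection that came before randomisation.

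A secondary question is balance within agencies. Therapists are assigned agency by agency. If the children share one list across agencies, the arms can drift apart within an agency even though they end at 60:60 overall.

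**Working it through.** The article gives no figure for predictability or for within-agency balance, so there is none to reproduce.

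**Inputs from the article.** Block size 4; 1:1 ratio, so 2 TDD and 2 TAU per block; 120 children, so 120 / 4 = 30 blocks; three agencies. **Assumed, because not given:** children per agency, 40/40/40, with 60/40/20 as the alternative.

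**1. Predictability with blocks of 4.** The observer knows the block size and sees every earlier allocation on the list, in order. There are 4! / (2! × 2!) = 6 equally likely orderings, so 6 × 4 = 24 positions.

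| Position in block | Chance it is forced | Chance the best guess is right |
|---|---|---|
| 1 | 0 | 1/2 |
| 2 | 0 | 2/3 |
| 3 | 1/3 (first two alike) | 1/3 × 1 + 2/3 × 1/2 = 2/3 |
| 4 | 1 | 1 |

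- Forced: (0 + 0 + 1/3 + 1) / 4 = 1/3, that is 8 of 24 positions, or 120 × 1/3 = 40 children on average.
- Best guess: (0.500 + 0.667 + 0.667 + 1) / 4 = 70.8%, against 50% with no information.

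**2. Who could reach that figure.**

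- *One list per agency:* local staff who see all their own allocations could reach one third. The arms within an agency then differ by at most 2 (half of an unfinished block of 4).
- *One shared list:* staff at a single agency see only part of each block and can deduce almost nothing with certainty. Only someone who follows all three agencies could reach one third.

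**3. Varying block sizes.** In 1,000 simulated lists of 120 with sizes 4 and 6 mixed at random, the observer knows the set of sizes and all earlier allocations but not the order of the sizes. The share known with certainty is about 5.5%. With sizes 2, 4 and 6 it is about 4.1%. Running the same method on blocks of 4 only returns 33.4%, in line with the exact 1/3.

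**4. Within-agency imbalance if there is one shared list.** Suppose children from the three agencies arrive in random order. The number on TDD among an agency's 40 then behaves like a draw of 40 from 60 + 60. The TDD-minus-TAU difference has standard deviation √(40 × 80 / 119) = 5.19.

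- The mean absolute difference is about 0.80 × 5.19 = 4.1.
- The difference moves in steps of 2, so the chance of 8 or more is about P(|Z| ≥ 7 / 5.19 = 1.35) = 18%.
- 20,000 simulations agree (4.1 and 18%) and give the result over all three agencies:

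| Assumed agency sizes | Some agency differs by ≥ 8 | Some agency differs by ≥ 10 |
|---|---|---|
| 40/40/40 | 37% | 19% |
| 60/40/20 | 32% | 16% |

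With 40 children, a difference of 8 means 24 against 16. Stratified by agency with blocks of up to 6, the difference cannot exceed 3.

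**The case against.** The strongest reply is that the key link is not in the text. The article does not say that the researchers who approach families learn earlier allocations, learn them in list order, or cover all agencies. Consent comes before allocation, an independent researcher allocates, and eligibility rests on SCARED-NL cut-offs with listed exclusions, which limits discretion over who qualifies. All of this stands. It makes the one third an upper bound for a particular observer and leaves selective approach or persuasion as the main route to bias. It does not remove the weakness, because the block size is stated and nothing described keeps past allocations from recruiters.

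Four stronger readings are tempting and are not supported.

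- *A third of allocations will be deduced.* The article supports only that they could be, by someone with the view described.
- *The children's scheme lacks agency strata and so clashes with the therapist assignment.* The article is silent, and a condensed protocol may leave strata to the full document. Assigning therapists by agency is equally compatible with a children's list kept by agency.
- *High local predictability and large agency imbalance occur together.* For local staff they need different list structures, as step 2 shows. They coincide only for an observer across agencies on one shared list.
- *One arm's therapists would be overloaded, or agency would bias the comparison.* The article gives 16 therapists in all, with no split by agency or arm and no caseloads. Chance imbalance under valid randomisation mainly costs precision and is not systematic bias.

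Unmasked reporting of the outcome is a separate source of bias. It does not make allocation easier to predict.

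**Conclusion.** The point holds in a conditional form. The firm part is a stated choice: one disclosed block size of 4 where treatment cannot be hidden from therapists or families. If a recruiter knows that size and can follow the list, up to 33.3% of allocations are known in advance and 70.8% can be guessed. The article neither establishes nor rules out that a recruiter has that view.

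The agency part is secondary. It applies only if the children share one list, and its 32% to 37% rests on assumed agency sizes and random arrival order. The threshold of 8 is a choice made for illustration. This is a weakness worth correcting because the remedy is cheap. It is not a contradiction in the protocol, nor evidence that selection occurred.

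**What to change.** Have the independent researcher generate the list with block sizes that vary at random, for example 4 and 6, and keep the sizes and their order from recruiting researchers and agencies. If the children's list is not already kept per agency, stratify it by agency to match the therapist assignment. The two changes belong together: stratifying while keeping a known block of 4 would let local staff see whole blocks and would make deduction at that agency easier.

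Varying sizes remove most certainty but not all guessing. A fixed block of 6, for comparison, still allows a best guess of 68.3%, so recruiters should also be kept from seeing a running record of allocations where practicable.

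The cost is a new list, with no burden on families. The downside is a slight overall imbalance from incomplete final blocks. With three agency lists and blocks of up to 6 it is bounded by 3 × 3 = 9 children, a bound approached only if all three lists stop at the worst point in the same direction. If recruitment has begun, the change can apply to the children still to be randomised.
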